### **Measurements – background, tools and discussion**

Being prepared for childbirth and parenthood and having available resources for meeting the demands may help parents cope with many concomitant situations.

In trials with subjective outcomes effect estimates are often exaggerated when there is inadequate or unclear allocation concealment (38). Blinding of participants and midwives is not feasible in this trial. In this situation it is desirable to specify at least one objectively assessed outcome, even if the outcome of most interest is subjective (38).

#### Primary outcome:

Epidural use during labour – using data from the hospital obstetric database (Birth)

Findings suggest that women who receive epidural analgesia experience more fear but not more pain, before the administration of epidural analgesia (39). Structured antenatal education may improve women's ability to cope during labour resulting in lower epidural rates (28).

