**Participants:** 2350 pregnant women  $\geq 18$  years old, recruited before 20+0 weeks gestation, due to give birth at Hvidovre Hospital. Being legally able and willing to provide signed consent, and being fluent in Danish.

**Intervention:** Women are randomised to receive:

1) A research-based birth and parenting program. The intervention consists of 4 sessions in small groups that last for 2,5 hours per session at 25, 33 and 35 weeks of gestation, and a post-natal session 5 weeks after expected due date.

2) Standard care (control group). The pregnant woman and her partner are offered two antenatal lectures in an auditorium.

The allocation of participants to the intervention will be 1:1 to the intervention and the control group.

**Methods:** Data will be collected via questionnaires at baseline, 37 weeks gestation, 9 weeks post-partum, 6 months post-partum and 1 year post-partum, via the hospital obstetric database, and via the national registers. Analyses will be intention to treat as well as per protocol analyses – sensitivity analyses comparing results from the two will be conducted. Subgroup analysis will be conducted in relation to personal and demographic characteristics.

Process evaluation will be conducted using questionnaires and qualitative interviews. The incremental societal cost of the intervention will be computed and compared to the measured outcomes in a cost-effectiveness analysis with epidural use during labour as the primary outcome. Direct health care costs and productivity cost in terms of labour market participation and short term absence will be calculated.

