sessions. Interest and participation in parenting programs is likely only to reach some parents, for instance uptake may be related to socioeconomic position (13, 34). It is possible but unknown if offering a parenting program in small local groups increases the likelihood of participation by parents who may otherwise be difficult to reach.

Cost-effectiveness analysis:

Finally the incremental societal cost of the intervention will be calculated and compared to the measured outcomes in a cost-effectiveness analysis. Direct health care costs as well as productivity costs in terms of labour market participation and sickness absence. For this we will use data from the obstetric database at Hvidovre Hospital, national registers and questionnaires.

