## **4. Selection and withdrawal of participants**

### **4.1 Inclusion criteria**

Expectant pregnant women and their partners  
≥ 18 years old  
Singleton pregnancy  
Due to give birth at Hvidovre Hospital.  
Able to speak and understand Danish  
Being legally able and willing to provide signed consent

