## **6. Assessment of outcome measures**

### **6.1 Efficacy variables**

Data will be collected via the hospital obstetric database, the national registers, and web-based questionnaires and collected in an electronic case record form (eCRF) at: baseline i.e. time point 0 (tp0) (<20 weeks gestation), 37 weeks gestation (tp1), 9 weeks (tp2), 6 months (tp3) and 1 year after expected due date (tp4).

The primary outcome is:

Epidural use during labour – data from the hospital obstetric database (tp2)

Secondary outcomes are:

Stress – perceived stress, parenting stress - questionnaire data (tp0,2,3,4)

Parenting alliance – questionnaire data (tp2,3,4)

Explorative outcomes:

Antenatal and Post-natal depressive symptomatology and anxiety – questionnaire data (tp0,1,2,3)

Breastfeeding - questionnaire data (tp0,1,2,3)

Use of healthcare services i.e.: for the parents obstetric intervention i.e. augmentation of labour, vacuum extraction, caesarean rate - data from the hospital obstetric database (tp2), and contact to

healthcare professionals for depressive symptomatology and anxiety, and unscheduled postnatal visits—questionnaire data (tp2,3). For the child i.e. neonatal readmissions to hospital, contacts to accident and emergency departments (A & E), GP and doctor on call during the child's first year of life (composite measure). Also use of the regional emergency phone line – data from the national registers (tp4).

Mental well-being – questionnaire data (tp 1,2,3)

Family medicine use – questionnaire data (tp2,3) and register data (tp4)

Smoking - questionnaire data (tp 1, 2)

Satisfaction with relationship and family break-ups - questionnaire data (tp 0,2,3), and data from the national registers on divorce and break-ups (tp4)

In this trial the intermediate outcomes of interest are:

Parenting resources: Trust in own ability to cope with/self-efficacy: 1) birth (tp1), 2) discharge (tp1) 3) parenting (tp2,4) breastfeeding (tp0,1); couple communication (tp0,1,2,3); social support/network (tp0,1,2,3)

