## 6.2 Method and timing

**Table 1: Assessment tools and outcome measures**

Baseline is time point 0 (tp0) (<20 weeks gestation), 37 weeks gestation (tp1), 9 weeks (tp2), 6 months (tp3) and 1 year after expected due date (tp4).

| Tools                                                                               | Outcomes                                          | Time points  |
|-------------------------------------------------------------------------------------|---------------------------------------------------|--------------|
| Primary measure                                                                     |                                                   |              |
| Hvidovre hospital obstetric database                                                | Epidural use                                      | • Birth      |
| Secondary Measures                                                                  |                                                   |              |
| Perceived stress scale                                                              | Stress                                            | • 0,1, 2,3,4 |
| Swedish Parenthood Stress Questionnaire (SPSQ) translated into Danish               | Parenting stress                                  | • 2,3,4      |
| The Parenting alliance measure                                                      | Parenting alliance                                | • 3,4        |
| Explorative Measures                                                                |                                                   |              |
| Single item question from the Longitudinal Copenhagen City Heart Study              | Stress frequency                                  | • 0,3,4      |
| Single item question from the Longitudinal Copenhagen City Heart Study              | Stress intensity                                  | • 0,3,4      |
| 10-item Edinburgh Postnatal Depression Scale                                        | Antenatal and Postnatal depressive symptomatology | • 0,1,2      |
| MDI, ICD-10                                                                         | Depressive symptomatology                         | • 3          |
| The Hopkins Symptom Check List (SCL-25) first 10 items (anxiety score, SCL-anxiety) | Anxiety                                           | • 1,2,3      |

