## 7.2 Statistical methods

Reporting will follow the guidelines of the CONSORT-statement. Statistical analyses will be intention to treat as well as per protocol. The level of significance will be 0.05.

The analysis of the primary binary outcome will be done using the generalised linear mixed model with distribution = binomial, link = logit.

If the percent missing cases > 5%, the results of this analysis will be subjected to a 'worst case' and a 'best case' scenario analysis of the potential impact of missing values. Assume a beneficial effect (less use of epidural analgesia) is noted in one group (group A) as compared to the other group (group B). A worst case scenario will then be constructed where missing values in group A are imputed by a "yes" to use of epidural analgesia and missing values in group B are imputed by a "no" to use of epidural analgesia. A corresponding best case scenario will also be constructed and the result under both scenarios will be computed.

Analyses (adjusted by baseline value and protocol specified variables) of perceived stress at 37 week gestation and for each of the other two secondary outcomes of the area under the curve (AUC) from 9 weeks to one year after due date will be done.

If the percent missing cases of an outcome is >5% and p of Little's test (1) < 5%, a number of datasets with observed values and predicted unobserved values necessary to produce an efficiency > 99% will be produced using multiple imputations (SAS version 9.3 or later)(2). The primary analysis will then be that based on these data sets.

Multiplicity will be dealt with as follows: the primary outcome will be tested at the 5% level. The p values of the remaining four tests will be adjusted using Hommel's procedure (Konietschke, 2012). In all events all observed p values will be reported.

For the secondary outcome measure 'Perceived Stress Scale' it will be tested using the general linear univariate model, whether the mean values differ between the two intervention groups at time 1 (37 week gestation), time 2 (9 weeks following birth), time 3 (6 months following birth), and time 4 (12 months following birth).

For the secondary outcome measure 'Swedish Parenthood Stress Questionnaire' it will be tested using the general linear univariate model, whether the mean values differ between the two intervention groups at time 2 (9 weeks following birth), time 3 (6 months following birth), and time 4 (12 months following birth).

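### Epidural use is read only from the Hvidovre obstetric database, so a woman enrolled there who gives birth elsewhere has no primary outcome

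*Protocol*

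**What the plan says.** Three places in the protocol define the primary outcome, and all name the same source. The list in section 6.1 has "Epidural use during labour – data from the hospital obstetric database (tp2"; the paragraph on the primary outcome has "Epidural use during labour – using data from the hospital obstetric database (Birth"; and Table 1 gives "Hvidovre hospital obstetric database" as the only tool for epidural use. The time label differs between the first of these and the other two, but the source does not.

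Eligibility is set by intention. Section 4.1 requires "Due to give birth at Hvidovre Hospital", and the Abstract describes women "recruited before 20+0 weeks gestation, due to give birth at Hvidovre Hospital".

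The trial has other data channels. Section 6.1 states that "Data will be collected via the hospital obstetric database, the national registers, and web-based questionnaires", and for the cost-effectiveness analysis section 2 says "For this we will use data from the obstetric database at Hvidovre Hospital, national registers and questionnaires". Section 3.8 provides a questionnaire 9 weeks after the due date with two e-mail reminders and, where possible, a phone call. Section 8 has each participant's CPR number checked. Neither the registers nor the questionnaires are named as a source for epidural use.

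Section 3.6 deals with miscarriage and stillbirth. No section deals with a live birth at another place. Missing primary outcomes are handled in section 7.2 by a rule that begins "If the percent missing cases > 5" per cent and leads to a worst-case and a best-case scenario. A further rule makes multiple imputation the primary analysis if, in addition, Little's test gives p below 5%.

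**The concern.** About half of pregnancy lies between enrolment and birth. In that time a woman can move, be transferred or give birth somewhere other than planned. A Hvidovre-only source has no record of her labour, so her outcome is missing because of how the source was fixed, not because the fact was never recorded anywhere.

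The outcome affected is the one the trial relies on most. Section 6.1 argues that, since participants and midwives cannot be blinded, at least one objectively assessed outcome is desirable. Epidural use is also the effect measure in the planned cost-effectiveness analysis. A later analysis plan can decide how to impute a missing value, but it cannot supply one that nobody arranged to collect.

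**Working it through.** **Inputs from section 7.1 and the Abstract.** Control rate 0.31; experimental rate 0.25; alpha 5% (taken as two-sided, which reproduces the stated figure); power 80%; 878 per arm; 2350 women in total at 1:1, so 1175 per arm.

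**Assumption.** A proportion m of primary outcomes is missing, equal in both arms. The protocol gives no rate of births elsewhere; I use 2–8%. The 5% trigger counts missing values from every cause, so births elsewhere add to withdrawals and other losses.

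**Step 1: the protocol's own figure.** With the pooled-variance formula for two proportions and mean rate 0.28:

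n = [1.960 × √(2 × 0.28 × 0.72) + 0.842 × √(0.31 × 0.69 + 0.25 × 0.75)]² / 0.06² = 878 per arm.

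This matches the protocol exactly. With complete data the expected z is 0.06 / √(2 × 0.28 × 0.72 / 878) = 2.80.

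**Step 2: power when only n(1 − m) women per arm have an outcome.**

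| m | 878 per arm | 1175 per arm |
|---|---|---|
| 0 | 80.0% | 90.0% |
| 2% | 79.2% | 89.4% |
| 5% | 78.0% | 88.5% |
| 8% | 76.6% | 87.5% |

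The loss of power is small throughout.

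**Step 3: the scenarios in section 7.2.** They run only above 5% missing, so m = 5% stands for the position just past the trigger (0.05 × 878 = about 44 women per arm).

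- Worst case, experimental arm: 0.25 × 0.95 + 0.05 = 0.2875.
- Worst case, control arm: 0.31 × 0.95 = 0.2945.
- Worst-case difference: 0.2945 − 0.2875 = 0.0070, or 0.7 points. The mean rate is 0.291, so z = 0.0070 / √(2 × 0.291 × 0.709 / 878) = 0.32. At 1175 per arm z = 0.37.
- Best case: (0.31 × 0.95 + 0.05) − 0.25 × 0.95 = 0.3445 − 0.2375 = 0.107, or 10.7 points.

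At m = 8% the worst case is −2.5 points and the best case 13.5 points.

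**Step 4: where the worst case changes sign.** The worst-case difference is 0.31(1 − m) − [0.25(1 − m) + m] = 0.06 − 1.06m. It is zero at m = 0.06 / 1.06 = 5.7%, about 50 women per arm at 878. This threshold does not depend on sample size.

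**Step 5: what recovery would do.** If all the missing outcomes were recovered, the bounds would collapse to 6.0 points, with power 80.0% (878 per arm) or 90.0% (1175 per arm).

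**The case against.** The case on the other side has real force.

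- **Size.** No document gives the rate of births elsewhere, so the 5% trigger may never be reached. At 2% missing the protocol runs no scenario at all, and a worst-case figure there would not be a result under its rules. This stands.
- **Power.** If 2350 women are randomised, 5% missing still leaves about 1116 per arm, more than the 878 planned. This stands: power is not the cost.
- **The scenarios do not replace the primary analysis.** Extreme bounds widen with missing data from any cause. A reader might infer that the primary result becomes uninterpretable. It does not: the scenarios are set beside the main estimate. What remains is that a sensitivity analysis the trial has committed to would say little.
- **Bias.** A reader might infer that the losses distort the comparison. Women who give birth elsewhere may well differ in their chance of an epidural, but the protocol gives no reason to expect their number or type to differ by arm, and no direction of bias can be shown.
- **Other sources.** A reader might infer that the trial already holds the same fact in another place. No section says that a register or questionnaire records epidural use; these are possible routes only. A questionnaire answer would also be unblinded self-report, given after the postnatal session at which birth experiences are shared, and so weaker than the objective record section 6.1 wants.
- **Only objective outcome.** A reader might also take epidural use to be the only objectively recorded outcome. It is not: obstetric interventions come from the same database, and other outcomes come from national registers.
- **Operational detail.** Retrieval of outside records could be described in data-management documents or in an analysis plan not shown here. That is possible, but the protocol does fix the source, the same way in three places, and read literally that excludes any other record.

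**Conclusion.** The point holds as a source fixed too narrowly. Enrolment is by planned place of birth, outcome capture is by actual birth at Hvidovre, and nothing bridges the two. Followed literally, every live birth elsewhere is a missing primary outcome.

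The direct cost in power is slight, about 2 percentage points at 5% missing. The cost that matters is in the missing-data scenarios: from just above 5% they would no longer support even the full planned effect, and above 5.7% the worst case points the other way. These figures assume the protocol's 31% and 25%, equal missingness in both arms, and a total share of missing values near or above 5%, which the protocol neither states nor rules out.

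This is an inexpensive improvement to make, not a defect that undermines the trial.

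**What to change.** In section 6.1 and Table 1, keep the Hvidovre database as the main source and add an order of back-up for randomised women with no birth record there:

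1. The birth record of the hospital where the woman gave birth, or a national register through her CPR number. Whether a register holds epidural use must be confirmed first.
2. As a last resort, one added item in the 9-week questionnaire on place of birth and epidural use (yes/no). Flag these values and use them only in a sensitivity analysis, because they are unblinded self-report.

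In section 7.2, apply the missing-value rules only to women still unresolved after these steps. Flag all second-source values and repeat the primary analysis without them.

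The cost is a few lines of protocol text, a slightly wider data request and one questionnaire item. The downside is a small number of values from a second source, which the flag and the repeat analysis make visible.

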#### Secondary outcomes:

Stress:

*The perceived stress scale* (PSS) will be used to measure global levels of perceived stress (tp 0,1,2,3,4). The PSS takes into account the individual's ability to cope (40). The scale was developed on the basis of appraisal theory (18) and was designed to “ . . . tap the degree to which respondents found

their lives unpredictable, uncontrollable, and overloading” (40). The PSS is widely cited, has been used in several studies of life stress, and has been translated into several languages. The PSS has been found to predict many adverse health outcomes (41). There has been some concern that psychological symptoms and the PSS may overlap in item content (40). However, the PSS has been shown to prospectively predict health outcomes independent of psychological symptoms (40, 42), supporting the discriminate validity of the PSS with regard to psychological symptoms (43). Despite limitations inherent in stress response measures and cautionary concerns about confounding with psychological symptoms, overall the PSS possesses good psychometric qualities and a respectable record of validity studies (41).

Parenting stress will be measured using *the Swedish Parenthood Stress Questionnaire* (SPSQ) (44) translated into Danish (tp2,3,4). The scale takes into account the individual's ability to cope and assesses parental stress with a sum score and subscale scores of incompetence, role restriction, social isolation, spouse relationship and health problems (44). Results from SPSQ have been related to physiological and psychological health, and socioeconomic and lifestyle factors (45). Furthermore significant correlations between SPSQ and clinical assessments of maternal stress and parental problems in responding to their child have been found (45).

Parenting stress has been shown to relate to negative child, parent, and family aspects e.g. lack of maternal emotional availability (46), maternal hostility (46), insecure child attachment (47, 48); parents' use of undesirable managerial techniques, (49) and more strict disciplinary style (50); child abuse and neglect, (51); depression in mothers, (52, 53), and poor marital quality (54).

#### *Parenting alliance*

Parenting alliance will be measured by the Parenting Alliance Measure (tp3,4) (55). It is believed that this is a more specific measure to the prediction of parenting behaviors than marital satisfaction because it recognizes that both parents can be involved, and function well, in the parenting role, and yet not be very satisfied with their personal relationship with each other (2, 55).

#### Explorative outcomes:

A health promoting antenatal program enhancing early parenting resources may affect a variety of outcomes in a positive way, however, due to the scope of this trial and power considerations the following outcomes will be explorative in nature.

#### *Stress frequency and stress intensity*

Two single item questions on perceived stress capturing how often an individual feels stressed and to what extent will be included (tp0,1,2,3,4). The questions are validated in a Danish population and derive from the Longitudinal Copenhagen City Heart Study (56).

#### *Antenatal and postnatal depressive symptomatology and anxiety*

In order to identify mothers (and fathers) with a possible emerging antenatal or postnatal depression, we will use the 10-item Edinburgh Postnatal Depression Scale (EPDS) (tp 0,1,2), and the Major Depression Inventory (MDI) (ICD-10) (tp 3). The EPDS is currently believed to be the best non-comprehensive screening tool, despite its relatively low predictive value and has recently been evaluated in a Danish population (57). The MDI is used to increase the diagnostic specificity and has similarly been used in a Danish population. The Hopkins Symptom Check List (SCL-25) first 10 items (anxiety score, SCL-anxiety) will be used to measure anxiety (tp 1,2,3).

An estimated 7% of expectant mothers suffer from depressive symptoms during the first trimester of pregnancy, increasing to 12-13% during the third trimester and 3 months postpartum (58, 59). Depression is associated with a high risk of anxiety, poor self-care, partner relationship problems (60), fear of childbirth (61), and poor obstetric outcomes (62). Furthermore maternal depression is associated with impaired mother-infant relations (63), an increased risk of feeding and growth problems (64), and regulatory and emotional problems (65-71) in the child.

The Newborn trial aims to address some of the risk factors associated with AND and PND e.g. self-efficacy, stress and social support (72, 73) which may reduce the occurrence. However, depression is a complex phenomenon with many pathways. As PND may have negative long-term consequences - especially if left untreated - how to recognize signs and symptoms of PND and how to act on these symptoms (e.g. contacting the general practitioner) is included as an important topic in the Newborn trial. It is therefore possible that a larger proportion of the intervention group will report and seek help for AND and PND.

